## Abstract

**Background:**

Endoscopic screening is the widely accepted screening strategy for esophageal squmaous cell carcinoma (ESCC). However, massive endoscopic screening is expensive and not cost-efficient, and novel pre-endoscopy detection used as a preliminary screening method arouses new concerns. We are planning to launch an artificial intelligence (AI) assisted sponge cytology for detecting esophageal squmaous high-grade intraepithelial neoplasia (HGIN) and above lesions. The aim of this trail is to investigate the efficiency of AI-assisted sponge cytology in population-based screening of early esophageal squmaous epithelial lesions.

**Methods:**

The study will be prospectively conducted in five regions with a high prevalence of ESCC. AI-assisted sponge cytology and endoscopic examination will be sequentially performed. Based on our previous data, at least 864 patients with esophageal HGIN and above lesions are needed to achieve enough statistical power. And, a calculated 112,500 individuals with high risks of ESCC will be recruited. In the first stage, each 24,000 participants who meet the inclusion criteria will be recruited on a voluntary basis. Setting pathological results as standard reference, diagnostic threshold and according performance of AI-assisted detection will be evaluated. A prediction model will be constructed by co-analyzing cytological results and relevant risk factors. Then, an external validation cohort will be used for validation of the model efficiency. Also, cost-efficiency analysis will be performed. This study protocol was registered on chineseclinicaltrial.gov (ChiCTR1900028524).

**Discussion:**

Our study will determine whether this AI-assisted sponge cytology can be used as an effective pre-endoscopy detection tool for large-scale screening for ESCC in high-risk areas.

**Supplementary Information:**

The online version contains supplementary material available at 10.1186/s12885-022-10220-3.

## Background

Esophageal cancer (EC) is the sixth leading cause of mortality and the seventh cause of morbidity among all cancers [1]. Esophageal squamous cell carcinoma (ESCC) is the predominant histological subtype of EC, and accounts for about 85% cases of EC [1, 2]. The overall 5-year survival rate of early ESCC is over 90% [3], but is less than 30% in advanced stage of disease [4]. This great gap in survival status indicates that it is important to adopt an early detection strategy to enable early diagnosis in areas with high risks of ESCC.

### Current status of ESCC screening

High risk factors of ESCC have been proposed, including family history of ESCC, heavy alcohol drinking, cigarette smoking, poor nutritional status, salted food preference, high temperature food preference, chemical carcinogen exposure and history of SCC of the head and neck or upper respiratory tract, et al. [5, 6].

Since critical risk factors have not been revealed, it is difficult to make significant breakthroughs in primary prevention of ESCC. So, secondary preventions aiming at early detection of precancerous lesions and intervention to prevent the disease progression have been considered appropriate strategies to focus on for ESCC control. Due to high sensitivity and accuracy, endoscopic screening has been widely used in population-based screening in China. A strategy of risk-stratified endoscopic screening has been proposed [7]. Endoscopic detection for ESCC and its precursor lesions is applied in 40–69 years aged permanent residents with one or more risks. However, the implementation of endoscopic screening for early ESCC and high-grade intraepithelial neoplasia (HGIN) is very costly because the demand of endoscopic screening from eligible individuals in high-risk areas of China is high. In addition, the incidence of ESCC, even in those regions with a high prevalence, is relatively low [5]. Hence, to develop a novel pre-endoscopy screening method will promote screening effectiveness and make it possible for large-population screening.

Although cytology has been used as pre-endoscopy detection, its role is limited due to poor diagnostic accuracy, low sensitivity and specificity [6, 8]. One main reason is that cytopathologists screen all slides manually for potentially interested lesions and it is not suitable for massive screening [9]. Therefore, the change of diagnostic manner will promote further application of cytological methods in screening of early ESCC and its precursor lesions. Similarly, a rigid diagnostic threshold for such detection should be established [10].

### Artificial intelligence (AI)-assisted cytological detection

We have introduced a novel sponge device (Shikang I®/Eso Heal I™, Froeasy Tech Co., Nanjing, China) for esophageal epithelial sampling [11, 12]. Also, we have reported our pilot performances [11, 12] of AI-assisted cytological detection for early ESCC and its precursor lesions by using a novel platform from Froeasy Tech Co., which is available at http://pms.n-ecdc.com/. Esophageal squmaous epithelial lesions can be classified into five levels, including normal squmaous cells, atypical squmaous cells (ASC), low-grade squamous intraepithelial lesion (LSIL), high-grade squamous intraepithelial lesion (HSIL) and squmaous cell carcinoma (SCC). The AI-assisted diagnosis has shown a diagnostic accuracy comparable to that by expert cytopathologists [11, 12].

We have reported a rapid work scheme for esophageal sponge cytology for detecting early ESCC [11]. The feasibility of this AI-based detection has been preliminarily established, as reflected by significant reduction of numbers of endoscopic examination for detecting esophageal lesions with clinical significance [11, 12]. In addition, the cost of community-based screening was significantly reduced by using this AI-assisted sponge cytology as pre-endoscopy screening [12].

Currently, role of AI-assisted sponge cytology in large-scale screening for esophageal HGIN and above lesions has not been confirmed. We assume that population-based screening can be facilitated by this AI-assisted cytology. Also, the cost-effectiveness of population-based screening may be improved.

### Study design

The project will be prospectively executed in five regions with a high prevalence of ESCC, including Huaian, Taizhou, Yangzhou, Suqian and Yancheng, in Jiangsu Province, China. Participants will be free of charge. Our primary objective is to investigate the efficiency of AI-assisted sponge cytology in population-based screening for esophageal HGIN and early ESCC. Secondary objectives include: (1) to establish the diagnostic threshold (i.e. ASC, LSIL [10]) in such cytological detection; (2) to construct a predicting model identifying individuals for further endoscopy examination by co-analyzing cytological features and relevant risk factors; (3) to analyze cost-effectiveness of this AI-assisted cytology in large-scale screening.

This is a two-stage, 5-year-period project. The flowchart of this study is listed in Fig. 1. The procedures include ESCC-related questionnaire collection, esophageal sponge sampling followed by AI-assisted diagnosis, and endoscopic examination and histopathlogical evaluation. Histopathological results are set as standard of diagnosis of esophageal HGIN and ESCC. In the first stage, population-based esophageal sponge cytology and endoscopic examination will be sequentially performed in four years. Data regarding ESCC-related risks, cytological outcomes, and endoscopic and pathological findings will be collected. Diagnostic efficiency and diagnostic threshold of this AI-assisted cytological diagnosis will be evaluated. By co-analyzing cytological outcomes and relevant risks, a prediction model will be constructed to identify individuals with histopathologically confirmed esophageal HGIN and above lesions. In the second stage, an external individual cohort will be enrolled. The prediction model will be validated, and the diagnostic performance will be assessed. Also, cost-efficiency analysis will be performed in two stages. Our working schedule and relevant results of this study are shown in Table 1.

**Fig. 1 Fig1:**
[figure not shown]
Flowchart of this study. ESCC: esophageal squmaous cell carcinoma

**Table 1 Tab1:** Working schedule of this study

Time length	Activities	Expected stage outcomes
1^st^ year	• Project announcement, planning and preparation • Course training and project coordination • Participant recruitment • Cytological screening &endoscopy • Data collection and transfer • Scientific visit and supervision	♦ Project initiation ♦ Screening 4,000 participants from each site
2^nd^ year	• Participant recruitment • Cytological screening &endoscopy • Data collection and transfer • Scientific visit and supervision	♦ Screening 8,000 participants from each site
3^rd^ year	• Participant recruitment • Cytological screening &endoscopy • Data collection • Scientific visit and supervision	♦Screening 8,000 participants from each site ♦ Interim report ♦ Preparation of the first publication
4^th^ year	• Participant recruitment • Cytological screening &endoscopy • Data collection • Data verification and analysis • Scientific conference	♦ Screening 4,000 participants from each site ♦ Data analysis assessment of diagnostic efficiency construction of prediction model cost-efficiency analysis
5^th^ year	• Participant recruitment • Cytological screening &endoscopy • Data analysis and archive • Project summary	♦ Screening 2,000 participants from each site ♦ External validation ♦ Publication of results ♦ Dissemination of results to public health agencies

Some key procedures, including course training, participant recruitment, esophageal sponge cytology and endoscopy, will be used in this study, and the details are listed as follows.Course trainingCourses about the program will be given to train community health workers, endoscopists and nurses prior to participant recruitment. Contents of training are as follows: (1) nature, purpose, ethical principles, study design and working scheme of this program; (2) questionnaire survey as a structured sheet of ESCC-related risks; (3) notices in esophageal sponge ingestion and sampling; (4) notices in endoscopic examination; and (5) quality control in cytological sampling and endoscopic biopsy.Participant recruitmentRecruitment announcements will specify the eligibility criteria, place and time of the screening. Information regarding this program will be spread through several approaches, including radio, television and paper announcements, public banners, free-accessible apps of hospitals and community health sectors, short messages by public health platform, and so on. Community health workers will also be specially trained to recruit participants. The free nature of this project will be emphasized.Potential eligible participants will be identified by a questionnaire survey for ESCC-related risks among 40–69-year-old permanent residents. Inclusion and exclusion criteria are listed as follows. Those who are deemed high risky of ESCC and voluntary to participate in this program will be recruited. Those who meet one or more of following items will be excluded: (1) < 40 years or ≥ 70 years; (2) pregnant women at the screening consultation; (3) prior history of esophageal cancer, esophageal stenosis, esophagectomy, esophageal varies or mental disorder; (4) positive for human immunodeficiency virus; (5) insufficient health to participate in this screening; (6) refusal to participate in this screening; (7) unwilling to undergo capsule sponge ingestion and/or endoscopy.Written consent is mandatorily required from each participant, and a copy of electronic record will be reserved. Subject confidentiality will be ensured by utilizing subject identification code numbers. ESCC-related risks from each individual will be collected.Esophageal sponge cytology and diagnosisEsophageal epithelial specimens will be collected by sponge device ingestion. And, cytological diagnosis will be performed in an AI-assisted manner. Key steps are listed as follows. (1) Esophageal epithelial specimens will be collected by an esophageal sponge device swallowed into the stomach [11, 12]. (2) The mesh along with specimens will be retrieved out of the mouth gently. Retrieval of sponge mesh will be attempted by each participant, and a standby health worker will be ready to provide help anytime necessary. The mesh containing specimens will be kept in cell preservation solution (Froeasy Tech Co., Chinese inventory patent is pending, ZL201810313809.8). (3)Specimens will be processed by liquid-based thin layer cell preparation technique. By using a sedimentation technology, 120 slides will be prepared for each specimen [11]. Feulgen-Eosin staining (Chinese invention patent, ZL 201,710,732,464.5) will be adopted. (4) All slides will be subjected to the AI-based diagnosis system. An automated squmaous epithelial cell classification will be given by AI-assisted diagnosis platform, and ASC and above cells will be automatically annotated by this system [11]. (5) Cytological outcomes of ASC and above will be confirmed by three expert cytopathologists independently [11]. As listed in the Supplementary material, specimen processing, slides preparation and staining, and AI-assisted diagnosis will be performed in a batch processing strategy.EndoscopyEndoscopy will be used to detect histopathologically confirmed esophageal lesions. An early endoscopy, which is completed within five working days, is recommended, but any time interval no longer than twenty-working-day is also acceptable. Participants who did not undergo endoscopy examination will be reminded by phone calls once every week; failing to undergo scheduled endoscopy examination within the time-frame will be excluded from this trial. Endoscopic examination will be performed under shallow sedation (midazolam, 0.1 mg/kg, ivggt; fentanyl, 1 μg/kg, ivggt) by competent (more than 5 years of experience in endoscopic procedures) or expert (more than 10 years of experience in endoscopic procedures) endoscopists at each study site. White light imaging and Lugol iodine staining will be sequentially performed to inspect the whole length of the esophagus and to evaluate suspected lesions. At least one biopsy will be taken from each suspected region. A normal solution of 5% sodium thiosulfate will be sprayed for reducing adverse events relevant to Lugol iodine staining. Histological diagnosis of esophageal biopsy will be classified into normal squamous epithelia, esophagitis, squamous cell hyperplasia, low-grade intraepithelial neoplasia (LGIN), HGIN, and ESCC.Data analysisDiagnostic accuracy of AI-assisted cytology for esophageal HGIN and early ESCC will be evaluated and compared to that of endoscopic detection. Diagnostic performances will be compared between different thresholds (ASC and above vs. LSIL and above). A prediction model for esophageal HGIN and early ESCC will be built based on co-analyzing with ESCC-related risks.Cost data will be collected since the start of the study regarding personnel remuneration, training and equipment costs. Further data will be collected regarding the time and cost required for each step of the project. The Markov model will be used for cost-effectiveness analysis.Diagnostic standardBased on our previous work [11, 12], cases diagnosed with ASC and above level lesion by AI system will be manually confirmed by two expert cytopathologists according to the Bethesda system [13]. Histopathological results from biopsies will be set as the gold standard for diagnosis of esophageal HGIN and early ESCC. Two expert pathologists who are masked of cytology results will provide consensual diagnosis.Supervision and quality control

Principal investigator, co-investigators or responsible researchers will visit each study site once every six months to give professional and scientific opinions for the aim of supervision of this project.

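### The history exclusions stop at esophageal cancer and esophagectomy, so known or endoscopically treated HGIN, the lower end of the target condition, can enter the accuracy analysis

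*Protocol article*

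**What the plan says.** The primary objective is stated under Study design: "Our primary objective is to investigate the efficiency of AI-assisted sponge cytology in population-based screening for esophageal HGIN and early ESCC". The target condition therefore begins at HGIN.

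The recruitment text in the same section gives the entry rule, "Those who are deemed high risky of ESCC and voluntary to participate in this program will be recruited", followed by seven numbered exclusions. Item 3 is the only one concerned with esophageal disease history: "prior history of esophageal cancer, esophageal stenosis, esophagectomy, esophageal varies or mental disorder". Items 1, 2 and 4 cover age, pregnancy and HIV. The remaining items read "5) insufficient health to participate in this screening; (6) refusal to participate in this screening; (7) unwilling to undergo capsule sponge ingestion and/or endoscopy".

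Biopsies are graded on a scale whose top three classes are "low-grade intraepithelial neoplasia (LGIN), HGIN, and ESCC". A case is defined by study histology alone: "Histopathological results from biopsies will be set as the gold standard for diagnosis of esophageal HGIN and early ESCC". Nothing requires the lesion to be newly found.

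The Background (Current status of ESCC screening) says that "endoscopic screening has been widely used in population-based screening in China" and, of the strategy in use, "Endoscopic detection for ESCC and its precursor lesions is applied in 40–69 years aged permanent residents with one or more risks".

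**The concern.** Item 3 removes people with known disease at the upper end of the target condition (cancer) but not at the lower end (HGIN). It also removes those treated by surgery, but not those treated endoscopically. Because the protocol's own scale keeps HGIN and ESCC apart, the words for cancer in item 3 cannot be stretched to cover HGIN. The Background makes earlier diagnosis plausible, since it describes endoscopic screening of people of the same age and risk type as those recruited here.

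Two groups can enter:

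- **Known HGIN still present, or residual or recurrent after endoscopic treatment.** Study biopsy confirms it and it counts as a case.
- **HGIN fully removed.** The person is a non-case, but with treated mucosa, which may affect specificity and the prediction model.

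At stake is what the accuracy estimate means. The study is to judge a test for population-based screening. If some cases were diagnosed before enrolment, sensitivity averages over two kinds of lesion. Lesions that are still present also raise apparent prevalence, yield and PPV, and these carry into the cost-effectiveness analysis. Because cases are rare, few such entrants are needed to form a noticeable share of them.

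**Working it through.** **1. The plan's own figures** (Sample size calculation). Inputs: sensitivity P = 0.90, Z = 1.96, permissible error 0.02, drop rate 20%, prevalence 1.2–1.5%, response rate 80%.

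- Cases: 1.96² × 0.90 × 0.10 / 0.02² = 864.4, stated as 864.
- After drop-out: 864 / 0.80 = 1,080.
- Participants at 1.2% prevalence: 1,080 / 0.012 = 90,000.
- Recruitment: 90,000 / 0.80 = 112,500.
- Second stage, error 0.06: 1.96² × 0.09 / 0.06² = 96.0 cases; 96 / 0.80 / 0.012 = 10,000.

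All reproduce. The point disputes none of them, and the fix changes none of them.

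**2. The eligibility text.** Taking the seven exclusions in turn, none names known HGIN or endoscopic treatment of it. The entry rule asks only for high risk and willingness. The case definition asks only for study histology. Followed as written, known HGIN that is still present is eligible and counts as a case.

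**3. How few entrants matter.** At 1.2% prevalence, 10% of cases is 0.10 × 0.012 = 0.12% of participants, about 1 in 833. At 1.5% it is 0.15%, about 1 in 667. In cases, 10% is about 86 of the 864 in the first stage and about 10 of the 96 in the second.

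**4. Effect on sensitivity.** Let f be the share of cases already known, S_new the sensitivity in new lesions and S_known that in known ones. Observed sensitivity is (1 − f) × S_new + f × S_known, so

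shift = f × (S_known − S_new).

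The document gives neither f nor S_known, so both are assumed. S_new is set at the planned 0.90.

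| f | S_known = 1.00 | S_known = 0.95 | S_known = 0.50 |
|---|---|---|---|
| 1% | +0.1 | +0.05 | −0.4 |
| 5% | +0.5 | +0.25 | −2.0 |
| 10% | +1.0 | +0.5 | −4.0 |
| 20% | +2.0 | +1.0 | −8.0 |

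(Shifts in percentage points.) The column at 0.50 stands for lesions that are hard to sample, for example small residual ones.

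**5. When the shift equals the 2-point margin.** With S_known = 1.00: f = 0.02 / 0.10 = 20%, or 173 of 864 cases. With S_known = 0.50: f = 0.02 / 0.40 = 5%, or 43 of 864 cases.

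**The case against.** The strongest reply is that nothing in the protocol is contradicted. The primary endpoint is diagnostic efficiency against histopathology, and a lesion confirmed on study biopsy is a valid true positive or false negative under it. The Background presents detection of precancerous lesions together with intervention, so people walking about with diagnosed, untreated HGIN may be few. The statement about existing screening is national; no coverage is given for the five recruiting regions, and the same paragraph stresses cost. Knowing where a lesion lies could help the endoscopist but not a swallowed sponge, so there is no firm reason to expect sensitivity to rise. All of this stands, and it limits the point to case mix and applicability, with a bias of unknown size and sign. It does not close the gap: the exclusions are a numbered list, which an article would not be expected to abbreviate, and the list stops one grade short of the target condition.

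Four stronger readings are tempting but unsupported:

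- *The objective concerns residents never screened before.* It speaks of population-based screening and does not restrict it in that way.
- *Removed HGIN counts as a case.* It does so only if residual or recurrent HGIN is found on study biopsy.
- *The same person can enter the first stage repeatedly.* Nothing printed permits it. The text is merely silent, as a condensed article may be, and the second stage specifies new individuals.
- *The questionnaire omits earlier endoscopy.* Its items are not listed in the article, so this cannot be known.

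**Conclusion.** The point holds as a mismatch between a stated eligibility rule and the stated target condition. The rule admits known HGIN as cases and fully treated HGIN as non-cases, so every accuracy measure, the yield, the cost-effectiveness analysis and the prediction model may mix previously diagnosed or treated disease with newly found disease.

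Its size cannot be settled from the document. With 90% sensitivity in new lesions and an assumed 10% of cases already known, the shift runs from +1.0 point if known lesions are always found to −4.0 points if half are found. The first lies inside the planned 2-point margin and the second outside it. A reader might infer that sensitivity is bound to be overstated. The document does not support a direction, since that depends on how readily the sponge samples known lesions. Unless prior diagnosis is recorded, the effect can be neither measured nor removed at analysis. This is a moderate point, worth correcting because correction is cheap.

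**What to change.** Extend exclusion 3 to a prior histological diagnosis of esophageal HGIN or prior endoscopic treatment of an esophageal squamous lesion, in both stages.

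For anyone already enrolled, record this history (if the questionnaire does not already capture it), omit those with it from the primary accuracy analysis and from model building, and report them separately.

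The cost is one eligibility clause, one recorded item and one table. A few participants are lost and the case yield may be slightly lower. The targets of 864 and 96 cases, and the recruitment figures derived from them, stay as they are.

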### Sample size calculation

According to our previous data, a sensitivity of 90.0% was present in AI-assisted esophageal HGIN and above lesions [11]. Sample size will be estimated by using the formula:$$\small {n=Z\alpha^2}P(1-P)/\delta^{2}$$

where *n* = required sample size, *P* = anticipated sensitivity. The confidence level is set as 95% in this study, and Zα = the corresponding standard normal deviate 1.96. And, δ = permissible error, which is set as 0.02. Therefore, 864 individuals with esophageal HGIN and above lesions are needed. Taking the drop rate of 20% into account, this number will be 1,080. Since the prevalence of disease is about 1.2–1.5% [5, 14], about 90,000 potential eligible participants are needed. Given a response rate at about 80%, participant recruitment will be about 112,500 individuals with high risks of ESCC. Therefore, we plan to carry out recruitment in 24,000 residents from each of the five regions in the first stage.

Sample size for validation is also calculated by using the abovementioned formula. The anticipated sensitivity, the confidence level, Zα and permissible error are set as 90%, 95% and 1.96 and 0.06, respectively. Therefore, 96 patients with esophageal HGIN and above lesions are needed. Taking the drop rate and the prevalence into account, about 10,000 participants are needed. Hence, 2,000 new individuals will be recruited from each study site in the second stage for the aim of validation of the predicting model.

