## Discussion

Since ESCC is a rare disease even in regions with an extremely high-risk [5], the cost of broad endoscopic screening project should be carefully evaluated. Recently, how to achieve quality improvement of screening has gained much interest [7, 15]. For the purpose of precise screening, this proposed project is aiming to explore the efficiency of an AI-assisted cytology as pre-endoscopy detection in population-based screening in high-risk areas. As shown in our previous results [11, 12], we believe that this trial will contribute to the establishment of a novel massive screening model for ESCC and similar kinds of diseases.

The project will be prospectively conducted in a real-world setting. According to designed research plan, all participants will undergo AI-assisted sponge cytology and endoscopic examination to minimize disease misclassification. Results of this trial will provide a convinced piece of evidence that how this technology can be integrated in massive screening for ESCC. In addition, the feasibility of this strategy as pre-endoscopy detection can be determined by cost-effectiveness analysis.

We suppose that results from this trial will demonstrate the feasibility of a reliable automated cytological detection for esophageal HGIN and above lesions, and the developed scheme will meet the great amount needs of large-scale screening in high-risk areas. In addition, this strategy will be superior to current endoscopic screening program by presenting a more precise, accurate outcome and a more economical procedure. Furthermore, a prediction model for identifying individuals with high-risks of confirmed lesions will be constructed, and will be prospectively validated. Based on relevant cytological outcomes and exposure of potential risks, this model will represent a higher efficiency than those models by evaluating ESCC-related risks only [16, 17].

Our results will be adopted as a promising complementary to current screening program in large-scale screening of ESCC in regions with a high prevalence. Decreased cost and saved medical sources can be achieved. Also, improved social and economic benefits can be brought up by the technique.

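### Participants who have cytology but miss endoscopy are dropped from the trial, leaving the primary sensitivity and specificity open to partial verification bias of unknown size and direction

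*Protocol article*

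**What the plan says.** All places are in the protocol article.

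- **Study design, Endoscopy.** Endoscopy follows cytology, preferably within five working days, with up to twenty accepted. Non-attenders are phoned weekly, and those "failing to undergo scheduled endoscopy examination within the time-frame will be excluded from this trial".
- **Study design, Participant recruitment.** Unwillingness to have the sponge or endoscopy is an exclusion at entry.
- **Study design, Diagnostic standard.** Histopathology is the reference. The two pathologists are masked to cytology. Nothing is said about participants, reminder callers or endoscopists.
- **Endpoints and Statistical analysis.** The primary endpoint is diagnostic efficiency against histopathology. Accuracy measures are reported with 95% confidence intervals, and no method is given for participants without endoscopy.
- **Sample size calculation.** The anticipated sensitivity is 90%, with a "permissible error, which is set as 0.02", so that "864 individuals with esophageal HGIN and above lesions are needed". Then: "Taking the drop rate of 20% into account, this number will be 1,080". A separate 80% response rate is applied afterwards.
- **Discussion.** By design, "all participants will undergo AI-assisted sponge cytology and endoscopic examination to minimize disease misclassification".

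**The concern.** The exclusion rule acts after the index test. Whoever misses endoscopy leaves the data set with a cytology result already in hand. If the chance of attending depends on that result, the verified participants no longer represent those screened. When cytology-positive people attend more readily, missed lesions among cytology-negative people drop out of the sensitivity denominator. Sensitivity is then overstated and specificity understated. Recruiting more people does not help: the interval narrows, but around the wrong value.

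The sample size section treats the 20% drop purely as lost numbers and does not say how much of it is missed endoscopy. Because the rule removes non-attenders altogether, it also removes the information needed to learn whether a bias exists and which way it runs.

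**Working it through.** **1. The plan's own figures reproduce.** n = 1.96² × 0.90 × 0.10 / 0.02² = 864.4 (stated 864). 864 / 0.80 = 1,080. 1,080 / 0.012 = 90,000. 90,000 / 0.80 = 112,500. The sample size arithmetic is not in dispute.

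**2. Formula for the complete-case estimate.** Let S be the true sensitivity, and v+ and v− the endoscopy completion rates in cytology-positive and cytology-negative diseased participants. Then

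observed sensitivity = S·v+ / [S·v+ + (1 − S)·v−].

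S = 0.90 is the protocol's anticipated value. The protocol does not give v+ or v−, so the values below are assumptions.

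| v+ | v− | Observed sensitivity | Bias (points) |
|---|---|---|---|
| 80% | 80% | 0.900 | 0.0 |
| 85% | 80% | 0.905 | +0.5 |
| 90% | 80% | 0.910 | +1.0 |
| 95% | 80% | 0.914 | +1.4 |
| 90% | 75% | 0.915 | +1.5 |
| 75% | 80% | 0.894 | −0.6 |
| 70% | 80% | 0.887 | −1.3 |

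**3. What a 2-point bias needs.** Reading 0.92 when the truth is 0.90 requires v+/v− = (0.92/0.08) / (0.90/0.10) = 1.278. There are two ways to get there.

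- *The 20% loss falls on the diseased (1,080 to 864).* This needs v− = 0.80 / (0.9 × 1.278 + 0.1) = 64.0% and v+ = 1.278 × 64.0% = 81.8%. Of 972 cytology-positive diseased participants, 795 are verified; of 108 cytology-negative, 69 are. 795/864 = 0.920.
- *The 20% is the overall loss among everyone screened, attendance depends on cytology alone, and every positive attends.* Then v− = (0.80 − q)/(1 − q), where q is the proportion cytology-positive. The bias reaches +2.0 only if q is at least 8%. The protocol gives no q. An assumed specificity of 90% with the stated prevalence of 1.2–1.5% fixes q near 11% (0.9 × 0.012 + 0.1 × 0.988 = 0.110; at 1.5%, 0.112). With q = 0.11, v− = 0.69/0.89 = 77.5%, and observed sensitivity is 0.90 / (0.90 + 0.10 × 0.775) = 0.921, a bias of +2.1 points.

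**4. Specificity, assuming a true 90%.** Observed specificity = 0.9·v− / (0.9·v− + 0.1·v+), if attendance among the non-diseased depends on cytology in the same way. At 90% versus 80% it is 0.72/0.81 = 88.9%. At 100% versus 77.5% it is 0.698/0.798 = 87.5%.

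**5. Effect on the interval (normal approximation, 864 verified cases).** At an observed 0.91 the standard error is 0.0097, and the nominal 95% interval covers 0.90 about 82% of the time. At 0.92 the standard error is 0.0092 and coverage is about 42%.

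**6. What adjustment recovers.** Weighting each verified case by the inverse of the completion rate in its cytology category, in the 81.8%/64% case: 795/0.818 = 972 and 69/0.64 = 108, so 972/1,080 = 0.900. Simulation of 1,080 diseased participants with known completion rates gives a mean of 0.900 and a half-width of about ±2.2 points, against ±1.8 for the unadjusted, biased estimate.

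**The case against.** The strongest objection is that nothing documents a link between attendance and cytology. Endoscopy is planned for everyone and is not triggered by a positive result. People unwilling to have it are excluded at entry, and the reminders are described identically for all non-attenders. Specimens are batch-processed, read by the AI system and then confirmed by experts, while endoscopy within five working days is preferred, so results may often not exist before endoscopy. The flowchart, the supplement and the full protocol are not shown and may say who learns the result and when. All of this stands.

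It rules out several stronger readings that a reader might infer:

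- *That the analysed subset is cytology-dependent and sensitivity is biased upward.* The text supports neither; zero or downward bias is equally compatible with it.
- *That the whole 20% drop, about 18,000 of 90,000, is missed endoscopy.* The protocol does not define the drop rate.
- *That the bias equals the full 2-point margin.* This needs the attendance patterns in step 3 of the working, for which no document gives a figure.
- *That the Discussion contradicts the 20% allowance.* One states design intent and the other expected attrition, and the two can coexist.

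The choice of adjustment method might also be left to an analysis plan that is not shown. The exclusion rule, however, is stated in the protocol itself. As worded, it takes out of the trial the people whom any later adjustment would need.

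**Conclusion.** The point holds as a risk created by an explicit rule, not as a demonstrated bias. Sensitivity and specificity as planned are complete-case estimates. They are unbiased if attendance is unrelated to cytology among the diseased and the non-diseased respectively. Sensitivity is too low if positives attend less and too high if they attend more.

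With a true sensitivity of 90%, assumed gaps of 5 to 15 percentage points in favour of positives give about +0.5 to +1.5 points. The planned permissible error of 2 points is reached only at the upper end: about 82% versus 64% attendance among the diseased, or all positives attending with about 11% positivity and 20% overall loss. All attendance rates, the positivity rate and the 90% specificity are assumptions. Even a 1-point bias matters when the stage-one sample is sized for ±2 points, and under the present rule neither its direction nor its size could be established afterwards.

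**What to change.** In the Endoscopy paragraph, replace exclusion from the trial with a statement that participants without endoscopy in the window stay in the data set, with their cytology and questionnaire data kept. In addition:

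- Report endoscopy completion by cytology category.
- State who knows the cytology result before endoscopy (participants, reminder callers, endoscopists).
- Say how much of the 20% drop is expected to be missed endoscopy.
- Estimate primary sensitivity and specificity with a verification-bias adjustment: Begg–Greenes, or inverse-probability-of-verification weighting by cytology category, site, age and risk factors. Give the complete-case estimate as a sensitivity analysis.

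No change to when results are released is proposed.

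The cost is protocol and analysis-plan wording and some further analysis of data that will have been collected anyway. There are two drawbacks. The adjustment is valid only if attendance is explained by recorded variables. The interval is also slightly wider, about ±2.2 against ±1.8 points in the strong-differential case. The change should be made before non-attenders' records are discarded, since they may not be recoverable.
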